**Methods and analysis:**

A total of 100 jaundiced newborns aged two weeks or younger will be included in this randomized, single-blind (the parents knew, but the neonatologists did not know), single-center controlled trial to receive either 10^9^ colony-forming units of AB-GG, Bb-12, M-16V, a combination of the three probiotics with blue-light phototherapy, or blue-light phototherapy alone. The experimental group will be treated with oral probiotics once daily for 30 days, while the control group will receive only blue-light phototherapy. The follow-up duration will last 30 days. The primary outcomes include changes in gut microbiota, metabolomics, and the incidence of phototherapy side effects, assessed after each phototherapy session, as well as on days 10, 20, and 30.

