### Purpose and hypothesis

The objective of this study was to explore whether AB-GG, Bb-12, and M-16V could contribute to neonatal hyperbilirubinemia treatment by regulating gut flora and metabolic imbalances, as well as reducing phototherapy side effects. We hypothesized that children receiving these three probiotics would exhibit a lower incidence of phototherapy side effects. Additionally, we speculated that the experimental group's fecal samples would demonstrate higher diversity and richness in intestinal microbiota compared to the control group. Moreover, we anticipated differences in the dominant bacteria, related metabolites, and metabolic pathways between the experimental and control groups.

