### Interventions

(1)Interventions: Neonates will be placed in a blue light treatment box (Ningbo David Medical Device Co., LTD, XHZ model) with the temperature set at 30°C and relative humidity at 55%. Phototherapy eye masks (Foshan Forman Medical Technology Co., Ltd., Yuesun Mechanical Equipment No. 20160015) and phototherapy diapers (Foshan Baojusheng Medical Equipment Co., Ltd., GB/T33280) will be used to cover the eyes and perineum. The treatment will involve LED blue light continuous irradiation with a wavelength of 425–475 nm. All neonates will undergo continuous phototherapy for 12 h, rest for 6–8 h, and then receive another 12 h of continuous phototherapy. The decision to continue with the next 12 h treatment session will depend on the changes in the neonate's jaundice condition.(2)Study drug and specifications: The patented probiotic combination (contains Bifidobacterium breve 10^9^, Lactobacillus rhamnosus 10^9^ and Bifidobacterium animalis 10^9^ per package) (invention patent, 202,010,414,426.7) will be added to the corresponding groups. The aforementioned drugs are freeze-dried powder, stored at room temperature, with a 30-month shelf life, and manufactured by China Taiwan Jinqiao Biological Co., Ltd. Probiotics intervention: the probiotics will be administered to jaundiced newborns requiring phototherapy. The experimental group will receive the corresponding daily probiotics during phototherapy. The probiotics will be mixed into the milk and consumed once a day, with a treatment course lasting for one month. Clinical study criteria will be controlled to determine the termination of the study.(3)Criteria for stopping the clinical study: (1) occurrence of serious adverse events occur that may be related to the use of probiotics; (2) if the planned interim analysis achieves the expected difference in efficacy and the intervention is observed to be significantly more effective in the trial group compared to the control group.(4)Adverse event observation

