
### Study procedure

Figure 1 illustrates the details of the research procedure. Parents will continue to receive information about the study for 30 days after enrollment when the newborn has confirmed that neonatal hyperbilirubinemia has met the criteria for phototherapy for the appropriate age, including during their regular follow-up visits to the hyperbilirubinemia clinic. Pediatricians participating in the study will sign written informed consent with parents. Subjects will be randomly assigned to receive AB-GG combined with phototherapy, Bb-12 combined with phototherapy, M-16V combined with phototherapy, all of the above probiotics combined with phototherapy, or phototherapy alone, following the method of a digital randomization list. The probiotic dose is 10^9^ colony-forming units (5 drops) administered orally once daily for 1 month. All subjects will be followed up for 1 month after the start of the intervention. Data and specimen collection on days 10, 20, and 30 will be completed during the outpatient follow-up for hyperbilirubinemia.

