The investigator will re-check the inclusion/exclusion criteria on the first day, perform patient management, conduct detailed physical and serologic examinations prior to phototherapy, and record the adverse events described in Table 1. They will collect stool and blood samples from the subjects. Subjects will receive the first 12 h of phototherapy and the assigned probiotics before phototherapy. After 12 h of phototherapy, researchers will observe phototherapy-related side effects (including body temperature, rash, stool frequency and shape, etc.), record information, collect stool samples, and measure TCB. On the next day, after 6–8 h of rest, the infant will receive a second 12 h phototherapy session while the assigned probiotics are orally administered, and the researchers will again assess and collect fecal samples. The same process will be followed for the third day, and if necessary, subjects may continue with the fourth and fifth 12 h phototherapy sessions, with at least 6 h of rest after each phototherapy session. Stool collection will still be required after each phototherapy session. Subjects will not require further phototherapy and will be discharged once they meet the discharge criteria.

Upon meeting the discharge criteria, the investigator will perform subject management, a detailed physical examination, serological testing, and evaluation of adverse events prior to discharge. Study follow-up on days 10, 20, and 30 will be completed at the outpatient follow-up for hyperbilirubinemia, during which stool and related data will be collected. Infants in the experimental group will continue to receive their assigned oral probiotics during hospitalization after enrollment and during outpatient follow-up for one month.

Stool samples weighing 500 mg and blood samples measuring 0.5 microliters were collected from each subject. The stool samples will be stored at −80°C after freezing, while the blood samples will be tested immediately. There would be no restrictions on the feeding patterns of both the experimental and control groups during the study. Parents are allowed to freely choose between breastfeeding, artificial feeding, and mixed feeding.

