### Endpoints

(1)Primary endpoint: significant reduction in the incidence of clinical side effects (i.e., diarrhea, rash, fever, vomiting, convulsions, feeding intolerance, etc.).(2)Secondary endpoints: after the addition of probiotics, the intestinal flora will be maintained in a stable state after phototherapy, and the changes in metabolic indicators; changes in jaundice (i.e., serum bilirubin, bile acid and transcutaneous bilirubin data), feeding status, changes in urine volume and weight, and vital signs during phototherapy

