•Data quality control and de-hosting sequence: KneadData software was used for quality control (based on Trimmomatic) and de-hosting (based on Bowtie2) of original data. FastQC was used to test the rationality and effect of quality control before and after KneadData.•Species annotation: Kraken2 and self-built microbial nucleic acid database (screening NCBI NT nucleic acid database and RefSeq whole genome database belonging to bacteria, fungi, archaea, and viruses) would be used to calculate the sequence number of the species contained in the sample, and then Bracken will be used to estimate the actual abundance of the species in the sample.•Common functional database comments: Starting from the quality control and the removal of host gene reads, HUMAnN2 software (based on DIAMOND) will be used to align the reads of each sample to the database (UniRef90). According to the correspondence between UniRef90 ID and each database, we will obtain the annotation information and relative abundance table of each functional database.•Based on the species abundance table and functional abundance table, PCoA and NMDS dimension reduction analysis (only species) and sample clustering analysis will be analyzed to obtain ɑ diversity, β diversity, bacterial symbiosis network results, etc. When grouping information is available, LEfSe biomarker mining analysis and metabolic pathway comparison analysis can be performed to mine the differences in species composition and functional composition between samples, count metabolite content and screen out characteristic metabolites. Mann-Whitney will be used for assessing gut microbiota and metabolites.•Annotation of resistance genes: Starting from the clean reads of removing host genes, DIAMOND software will be used to compare and annotate the quality control of each sample and the reads of removing host genes with the antibiotic resistance gene database CARD, and the abundance distribution of resistance genes could be obtained.•metabolome analysis using the R language MetaboAnalystR package. This package enables the quantification of metabolite content and the identification of characteristic metabolites. MannWhitney U and Kruskal-Wallis tests will be used to analyze differences in gut flora and metabolites between groups.

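### The stool analyses as described count the fed probiotic species as part of the infant's flora, so a hit on those species, and part of any diversity difference, can reflect the dose alone

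*Protocol article*

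**What the plan says.** **Dosing and sampling.** The abstract states: "The experimental group will be treated with oral probiotics once daily for 30 days". Interventions describes the combination product, which "contains Bifidobacterium breve 10^9^, Lactobacillus rhamnosus 10^9^ and Bifidobacterium animalis 10^9^ per package". Under Study procedure, "All subjects will be followed up for 1 month after the start of the intervention", and "Data and specimen collection on days 10, 20, and 30 will be completed during the outpatient follow-up for hyperbilirubinemia". Stool is also taken after each phototherapy session. The same section confirms that dosing runs on through the outpatient visits: "Infants in the experimental group will continue to receive their assigned oral probiotics during hospitalization after enrollment and during outpatient follow-up for one month". Under Allocation concealment, C0 is phototherapy alone, and the eligibility criteria bar earlier use of microecological agents.

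**Aims.** Purpose and hypothesis expects that "the experimental group's fecal samples would demonstrate higher diversity and richness in intestinal microbiota compared to the control group", and that the dominant bacteria will differ between groups. Endpoints lists as secondary that "the intestinal flora will be maintained in a stable state after phototherapy". The abstract counts microbiota change among the primary outcomes; the point applies under either ranking.

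**Pipeline.** Statistical analysis and bioinformatics analysis goes step by step. KneadData does quality control and host removal. Kraken2 and Bracken give species abundance. HUMAnN2, starting again from the cleaned reads, gives functional abundance. These tables feed alpha and beta diversity, PCoA and NMDS, a network analysis and group comparisons: "LEfSe biomarker mining analysis and metabolic pathway comparison analysis can be performed to mine the differences in species composition and functional composition between samples". Mann-Whitney and Kruskal-Wallis tests compare groups. No step removes the administered species or reports them separately.

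**The concern.** The treated infants swallow the organisms that the species table then counts. A fed species that is rare in controls will appear as a difference in dominant bacteria or as a LEfSe biomarker, whether or not anything else in the gut has changed. The four probiotic arms receive different organisms, so they can also differ from one another for this reason alone. Diversity and between-sample distance carry part of the same signal.

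What is at stake is the mechanistic conclusion. The protocol wants to say that probiotics regulate a flora disturbed by phototherapy. With only the unfiltered table, a reader cannot separate that from the trivial fact that the infant was dosed. The side-effect endpoint is not affected.

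**Working it through.** **Inputs from the protocol.** Three dosed species, one in each of T1 to T3 and all three in T4; daily dosing for 30 days; stool after each phototherapy session and on days 10, 20 and 30; 20 infants per group. The protocol gives no figure for the microbiota endpoints. The 20 per group was set for side effects (47% against 10%) and reproduces with the unpooled two-sided formula: (0.47×0.53 + 0.10×0.90) × (1.96 + 0.84)² / 0.37² = 0.3391 × 7.85 / 0.1369 = 19.4, so 20. It is used below only as the group size.

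**Assumed inputs, because the documents give none.** The dosed share of reads p, the resident Shannon index H, the spreads, and how often controls carry the species. Throughout, the rest of the flora is held unchanged, so any difference found is due to the dose.

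**1. Timing.** Follow-up and dosing both last one month from the start. Day 30 is at the latest the end of dosing, so no post-baseline stool is off treatment. The first-day stool is read here as taken before the first dose.

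**2. A single fed species.** Absent in 20 controls and present in 20 treated infants: exact two-sided Mann-Whitney p = 2/C(40,20) = 2/137,846,528,820 = 1.5e-11. Multiplying by 1,000 for an illustrative number of taxa still leaves 1.5e-8. If controls may carry the species (median 2% of reads in carriers, log-SD 1.5; dosed share with the median shown, log-SD 1; 3,000 simulated trials), the rejection rates at the 5% level are:

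| Control prevalence | p = 0.1% | p = 1% | p = 5% | p = 10% |
|---|---|---|---|---|
| 0% | 100% | 100% | 100% | 100% |
| 30% | 82% | 97% | 100% | 100% |
| 70% | 11% | 56% | 99% | 100% |
| 100% | 6% | 35% | 95% | 99.9% |

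**3. Shannon index.** Adding a new species at share p gives (1-p)H + h(p), with h(p) = -p ln p - (1-p) ln(1-p). The shift is h(p) - pH. At p = 0.1, h = 0.325, so the shift is +0.23 for H = 1.0 and +0.13 for H = 2.0. At p = 0.5, h = 0.693, so it is +0.19 and -0.31. Three equal strains with total share p add p ln 3: the shift is then +0.23 to +0.33 at p = 0.1 and +0.24 to +0.74 at p = 0.5. For one strain and H = 1.5:

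| p | Shift | Rejection, SD 0.3 | Rejection, SD 0.5 |
|---|---|---|---|
| 1% | +0.04 | 7% | 6% |
| 5% | +0.12 | 24% | 11% |
| 10% | +0.18 | 45% | 18% |
| 20% | +0.20 | 60% | 26% |
| 50% | -0.06 | 13% | 8% |

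**4. Richness.** The shift is at most +1 in T1 to T3 and +3 in T4. With mean 30 and SD 3, 5 and 10, rejection is 17%, 9% and 5% for +1, and 86%, 44% and 15% for +3.

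**5. Distance.** Between a profile q and (1-p)q plus a new species at p, the shared abundance is 1-p, so the Bray-Curtis distance equals p.

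**6. With the fed species removed.** Under the same assumption of unchanged flora, rejection for Shannon and richness returns to 4% to 6%, as it must by construction.

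**The case against.** **Retention is inferred.** The article never says that fed species are kept, and taxon filtering could sit in an analysis plan that is not shown. That is fair as far as it goes. But the pipeline is set out in order, with its removals named, and the species table passes directly to the analyses. The point concerns what that sequence fixes.

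**The whole community is a legitimate target.** The protocol speaks of regulating gut flora and of diversity in stool. It does not restrict the question to resident organisms, and establishment of a fed strain may be part of the effect. Removal at species level would also delete any native organisms of the same species (B. breve is the plausible case), and renormalising hides displacement of residents. This stands, and it is why the filtered table should not replace the unfiltered one as the main analysis.

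**Stronger readings that the documents do not support.**
- A reader might infer that diversity and richness are bound to differ. The working shows near-nominal rejection for +1 species at larger spreads, and a Shannon effect that varies in size and sign.
- A reader might infer that T4 must look more diverse than T1 to T3. For Shannon, that needs equal strains and the same total share in each arm, and neither is stated.
- A reader might infer that the dose pushes the richness hypothesis and the stable-flora endpoint in opposite directions. The protocol does not define stability as distance from the pre-dose sample, so that conflict depends on a definition it does not give.
- A reader might infer that the functional tables inherit the problem from the species table. They are built separately from the cleaned reads; they are affected because those reads include the fed genomes.

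**Conclusion.** The point holds as a limit on interpretation; no stated figure in the protocol is wrong because of it. All post-baseline stool in T1 to T4 is collected on treatment, and the described pipeline leaves the fed species in. A LEfSe or dominant-bacteria difference on a fed species that is rare in controls is near certain and shows only exposure. It weakens as controls carry the species more often and as the dosed share falls, down to 6% rejection when all controls carry it and the share is 0.1%.

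Diversity and distance can also shift with no change in the other flora. Under the assumed ranges, rejection runs from 6% to 60% for Shannon and from 5% to 86% for richness, with the high richness figures confined to the combination arm. The Shannon artefact can favour or oppose the stated hypothesis. All these sizes rest on assumed shares, spreads and prevalences. The algebra and the timing do not. Real changes in the remaining flora would also be detected, so the microbiota endpoints reflect the dose in part, not wholly.

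**What to change.** 1. Keep the whole-community analysis. Pre-specify beside it the same between-arm diversity, ordination, network and LEfSe analyses with B. breve, B. animalis and L. rhamnosus removed from every sample in all five arms and the table renormalised.
2. Draw conclusions about flora other than the fed species only from results that hold in the filtered table.
3. Report the abundance of the three species separately in every arm, as exposure in T1 to T4 and as possible carry-over in C0. Do not count LEfSe hits on them as biomarkers of effect.
4. Label pathway results as including reads from the fed genomes, or repeat them with those reads excluded. Filtering the species table alone does not clean the HUMAnN2 output.
5. Describe the day 1 to day 30 results as on-treatment.

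The cost is a second set of analyses on data already produced, plus wording; no new samples or visits are needed. The drawback is that species-level removal also drops native B. breve, and the unfiltered result is kept for that reason. Fixing both analyses before results are seen also prevents a later choice between the two tables.

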**Figure 1 F1:**
[figure not shown]
Flow chart of the trial.

The arrangements for enrollment during hospitalization and outpatient follow-up after discharge are shown in Table 1. At the beginning of the study, all eligible newborns will undergo a detailed physical examination. The pediatrician will record comprehensive general information (including the mother's prenatal examination, fetal condition, birth history, medication history, feeding history, length, weight, etc.). Jaundice indicators will be recorded before enrollment, blood samples will be collected (for thyroid function and serum bilirubin), and any adverse events will be documented.

**Table 1 T1:** Enrollment and follow-up items during hospitalization and after discharge.

Inspection schedule									
Time window	Enrollment, D0	Phototherapy for 12 h, D1	Rest for 6–8 h after phototherapy, D1	Phototherapy for 12 h, D2	Rest for 6–8 h after phototherapy, D2	Phototherapy for 12 h, D3	Rest for 6–8 h after phototherapy, D3	On the day of discharged, D4	Post-discharge, D10, D20 and D30
Informed consent	X								
Inclusion and exclusion criteria	X	X	X	X	X	X	X	X	X
Feeding situation	X	X	X	X	X	X	X	X	X
Give light therapyintervention		X		X		X			
Random givento probiotics		X		X		X		X	X
check-up	X	X	X	X	X	X	X	X	X
vital sign	X	X	X	X	X	X	X	X	X
Weight/urine output	X	X	X	X	X	X	X		X
Serum examination 1		X							
Systemic assessment	X	X	X	X	X	X	X	X	X
Percutaneous bilirubin determination	X	X	X	X	X	X	X	X	X
Stool assessment andSystemic assessment		X		X		X		X	X

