### Randomization

(1)The randomized scheme of this experiment will be as follows: 100 cases are planned to be enrolled and divided into 5 groups: C0 (pure phototherapy group), T1 (treatment group 1), T2 (treatment group 2), T3 (treatment group 3) and T4 (treatment group 4), with 20 cases in each group.(2)The random system parameters will be set as follows:
•Random system: Taimei Medical eBalance random system•Random method: block random•Block length: 5•Number of blocks: 20•Random number: P001–P100.

The random operation steps would be as follows: The random-related parameters are determined according to the project's random scheme. The eBalance stochastic system is configured according to random parameters. The eBalance random system generated a random grouping table according to the configuration (calling SAS software). The eBalance random system exported the random grouping table.

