### Statistical analysis and bioinformatics analysis

In SPSS software (version 22.0), chi-square distribution and mean value analysis will be used to analyze the characteristics of subjects. The Mann-Whitney test will be used to compare differences between groups, and the Wilcoxon test will be used to analyze differences in alpha diversity. There are five main steps in bioinformatics analysis:

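### Cross-sectional rank tests, named inconsistently, are fixed for microbiota and metabolite outcomes defined as change over repeated visits in five arms, so baseline and feeding data go unused and precision is lost

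*Protocol article*

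**What the plan says.** The section Statistical analysis and bioinformatics analysis names the tests three times, and the statements differ:

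- In general, and for alpha diversity: "The Mann-Whitney test will be used to compare differences between groups, and the Wilcoxon test will be used to analyze differences in alpha diversity". It does not say whether Wilcoxon means the rank-sum or the signed-rank test.
- For flora and metabolites, in the item on species and functional tables: "Mann-Whitney will be used for assessing gut microbiota and metabolites".
- For the same data, in the metabolome item: "MannWhitney U and Kruskal-Wallis tests will be used to analyze differences in gut flora and metabolites between groups".

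The same section adds that "LEfSe biomarker mining analysis and metabolic pathway comparison analysis can be performed" once grouping information is available.

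The design behind these tests is as follows. Under Randomization, "100 cases are planned to be enrolled and divided into 5 groups", with 20 infants in each, in blocks of five and with no stratification stated. The Abstract lists changes in microbiota and metabolome among the primary outcomes; the Endpoints section lists flora stability after phototherapy and metabolic changes as secondary. The stool row of Table 1 is marked on D1, D2, D3, D4, D10, D20 and D30. On feeding, the Study procedure section says: "Parents are allowed to freely choose between breastfeeding, artificial feeding, and mixed feeding". The row "Feeding situation" in Table 1 is marked in every column. Age at entry may be anything up to two weeks.

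**The concern.** The question asked is longitudinal: does the flora of an infant given probiotics move differently from that of an infant given phototherapy alone? The tests named are cross-sectional. Mann-Whitney and Kruskal-Wallis compare one value per infant between arms. They accept no covariate and have no place for several stools from the same infant. Feeding type and age in days are recorded and can plausibly explain part of the variation between infants, but no named analysis uses them.

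The inconsistent naming matters too. With five arms, it must be clear whether a five-group test comes first and which pairwise contrasts follow. The article links the two nowhere.

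Finally, any analysis of change needs a value from before treatment. The text and Table 1 do not show that sample in the same way. If it is missed at the bedside, no later analysis plan can recover it.

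**Working it through.** **The plan's own figure.** The only sample size given is 20 per group, derived for digestive side effects (47% against 10%, type I error 0.05, power 0.80). With two-sided 0.05 and unpooled variance:

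n = (0.47×0.53 + 0.10×0.90) × (1.960 + 0.842)² / 0.37² = 0.3391 × 7.85 / 0.1369 = 19.4, i.e. 20.

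The figure reproduces (without using the stated 0.05 margin). It says nothing about microbiota or metabolites, for which the article gives no precision statement.

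**Are the named tests valid?** In 2,000 simulated null trials with five arms of 20 infants, one feature and one visit:

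| Procedure | Type I error |
|---|---|
| One Mann-Whitney contrast | 0.047 |
| Kruskal-Wallis, five arms | 0.047 |
| Any of four Mann-Whitney contrasts with the shared control, uncorrected | 0.149 |

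Four independent tests would give 1 − 0.95⁴ = 0.185; sharing the control arm lowers this to about 0.15. So each test holds its level, and a set of uncorrected contrasts does not.

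**What does leaving out baseline cost?** The documents give no correlation r between the day-1 value and a follow-up value, so 0.3, 0.5 and 0.7 are assumptions. Linear adjustment multiplies the variance by 1 − r², and the equivalent number per arm is 20/(1 − r²). The detectable difference at 80% power, two-sided 0.05, for a rank test with 20 per arm is (1.960 + 0.842) × √(2/20) / √0.955 = 0.91 SD, where 0.955 is the efficiency of the rank test under normality. Adjustment multiplies it by √(1 − r²).

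| r (assumed) | 1 − r² | 20/(1 − r²) | Detectable difference |
|---|---|---|---|
| not used | 1.00 | 20 | 0.91 SD |
| 0.3 | 0.91 | 22.0 | 0.86 SD |
| 0.5 | 0.75 | 26.7 | 0.79 SD |
| 0.7 | 0.51 | 39.2 | 0.65 SD |

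These factors apply to linear adjustment of a roughly normal (transformed) outcome. They are not shown for sparse taxa.

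**Would change scores do instead?** A rank test can be run on follow-up minus baseline. With equal variances, a change score has relative variance 2(1 − r): 1.4, 1.0 and 0.6 at r = 0.3, 0.5 and 0.7. Adjustment gives 0.91, 0.75 and 0.51, which is smaller each time.

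**The baseline stool.** The Study procedure text describes a stool collection on the first day ahead of its account of the first dose and session, and another stool after that session. Table 1 has no stool mark at D0 and one mark in the D1 phototherapy column. Two samples in the text thus meet one mark in the table.

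**The case against.** The strongest reply is that this is a condensed article and a fuller analysis plan may exist. Covariates, the main time point and control across features commonly sit there, so silence on them is no fault. That stands: the article does not refuse false-discovery control, and its absence is not counted against it here. What remains is that the article positively names the tests, and names them in conflicting ways. A later plan with a repeated-measures model would have to override that text.

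A second reply is that the tests suit the design better than it first appears. Kruskal-Wallis is a five-group test, Wilcoxon may mean the paired signed-rank test, and rank tests can be applied to changes. All true, so it would be wrong to say that only two-group tests are planned. But the article does not say which Wilcoxon is meant, a paired test within one arm does not compare arms, and change scores recover less precision than adjustment.

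A third reply concerns Table 1. The D1 column also holds the serum examination, which the text places before phototherapy, so that column may include pre-session procedures. This is a fair reading, and it makes the point one of clarity rather than of a sample certainly missing.

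Three stronger readings are tempting, and the documents do not support them:

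- **Variance understated because visits are pooled.** No section says that repeated stools will be treated as independent.
- **Reported features mostly chance findings.** That depends on the number of features, on how many truly differ and on whether a correction is used. The article gives none of these.
- **Feeding imbalance biases the comparison.** Allocation is random, so the 5% error rate already covers chance imbalance in feeding or age. Ignoring them costs precision and does not inflate error.

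**Conclusion.** The point holds as a mismatch between outcome and method. The tests named do not use the day-1 value as a covariate, the recorded feeding type or the repeated structure of the data, and the statements on which test applies disagree. The expected cost is lost precision: with linear adjustment, 20 per arm would act like about 22 to 39 for assumed correlations of 0.3 to 0.7. The true gain depends on a correlation the documents do not give and on a suitable transformation. Per-visit tests of a single feature are valid; the type I error of about 0.15 per feature and visit arises only if four contrasts with control are run without correction. The point carries more weight if these outcomes are primary, as in the Abstract, than if they are secondary, as under Endpoints. It should be settled before the analysis; the baseline sample should be settled while recruitment is still open.

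**What to change.** 1. **Alpha diversity and key metabolites (suitably transformed).** Replace the rank tests by a mixed model with arm, post-baseline visit and their interaction and a random infant effect, adjusted for the pre-dose stool value, feeding type at enrolment and age in days. Name one main time point in advance; its choice is for the trial team.
2. **Individual taxa, pathways and metabolites.** State one rule in place of the three sentences: an omnibus five-arm test, then contrasts of each probiotic arm with control, with Benjamini-Hochberg control within each feature class. Say at which step the correction applies.
3. **Wilcoxon.** If it is kept anywhere, say which form is meant.
4. **LEfSe.** Label it exploratory.
5. **Table 1.** Reconcile it with the Study procedure text so that the stool taken before the first dose and first session is shown explicitly, separately from the one after that session.

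The cost is wording, one entry in Table 1 and modest analysis time, using data already scheduled for collection. The downside is that fewer features will reach the reporting threshold.
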